### Effectiveness analysis

The effectiveness of the IMPROVA programme will be evaluated based on improvements in overall mental health. Specifically, the primary analysis of effectiveness will be reflected in a reduction in the total SDQ score. In addition, effectiveness will be assessed through improvements in the secondary outcomes, as specified in a preceding section.

A linear mixed-effects model will be used to assess the effectiveness of the intervention on continuous outcomes (SDQ total score) measured across three assessment points, and generalised estimating equations will be used for categorical outcomes. Adolescents will be nested within schools, and schools will be nested within the four countries. A complementary analysis will include all four time points to evaluate the potential intervention effects at follow-up.

The model will include fixed effects for time, group (intervention vs control), and their interaction (group×time), which captures the differential change over time attributable to the intervention. The interaction term will be the main parameter of interest for assessing intervention effectiveness. To account for the multilevel design, the model will include a random intercept for each participant to account for repeated measures, a random intercept for each school to adjust for within-school clustering, and a fixed effect for country to control for systematic differences across national contexts. Other covariates associated with the outcome may be included in the model as fixed effects, depending on the objective. All models will be adjusted for the sex and age of the student.

The effectiveness analyses will be carried out following the intention-to-treat principle. In addition, a complete case analysis will be conducted as a sensitivity analysis to assess the robustness of the findings. Differences between included and excluded participants will be examined to explore potential bias due to missing data.

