### Sample size

Adolescents are the main unit of analysis of this RCT. Statistical power calculations indicated that 6000 adolescents are necessary to detect small differences (d=0.30) in mental health scores between the control and intervention groups, with 80% power. This calculation considered that schools would have 200 students (cluster size), two measurements, an aggregated intra-class correlation of schools and countries of 0.20, α=0.05, and 50% refusal to participate and loss to follow-up. A total of 6000 adolescents will also allow for stratifying the effectiveness analysis per one characteristic (eg, sex (male, female), socioeconomic status (higher, medium, lower)).

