### Effect modification analysis

We will also evaluate whether the intervention effect varies according to certain characteristics such as participants’ sex, age, country, socioeconomic status, school type, and mental health status at baseline. These analyses will involve testing for statistically significant interaction effects between the intervention and potential moderators within linear mixed models.

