### Mediation analysis

Mediation analysis will be performed using structural equation modelling to assess whether the effect of the intervention on the primary outcome is mediated by one or more intermediate variables (mediators) such as the secondary outcomes or other variables.

All available data will be included under the assumption that data are missing at random. All statistical tests will be two-sided, and a p value ≤0.05 will be considered indicative of statistical significance. Effect estimates will be reported with corresponding 95% CIs to indicate the precision of the estimates. The analysis will be conducted with SAS (V.9.4) and/or R software.

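### The primary SDQ model estimates a difference in change from baseline; efficient adjustment for baseline SDQ would be more precise, by about 1–2% to 10–15% of variance depending on unstated correlations

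*Protocol article*

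**What the plan says.** Under Effectiveness analysis, the article specifies a linear mixed model for the SDQ total score over three assessment points. Follow-up enters only a complementary four-point analysis, so the three are baseline, mid-term and postintervention, and baseline SDQ is a response. Fixed effects are time, group, group×time and country; random intercepts are for pupil and school. The interaction, "which captures the differential change over time attributable to the intervention", is the main parameter. On covariates it says: "All models will be adjusted for the sex and age of the student". Other covariates linked to the outcome are allowed, but baseline SDQ is not among those named. Nothing constrains the groups to be equal at baseline.

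Outcomes and assessments makes postintervention the primary endpoint. Effect modification analysis lists "mental health status at baseline" among the moderators. Under Blinding, randomisation and allocation concealment, schools were randomised before baseline, without blinding afterwards. Under Intervention group, platform access opened only after baseline assessment.

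**The concern.** A change score subtracts the whole baseline value, including the part that does not predict the later score. An efficient adjustment removes only the predictive part. Baseline SDQ was measured before platform access, so it can serve as a covariate. With 51 schools recruited against a target of 64, precision that is available from data already collected is worth having.

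A second, conditional issue concerns moderation. If baseline SDQ is itself the moderator and the response still includes baseline, the same value stands on both sides of the model.

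**Working it through.** **Inputs from the article.** Sample size states power to "detect small differences (d=0.30) in mental health scores between the control and intervention groups, with 80% power", α=0.05, 200 students per school, two measurements, "an aggregated intra-class correlation of schools and countries of 0.20" and "50% refusal to participate and loss to follow-up". Tests are two-sided (Mediation analysis). School recruitment and selection gives 51 schools in total, although the country counts listed add to 50. Analysed pupils per school: 6000 × 0.5 / 51 ≈ 59.

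**Assumed, because not stated.** Within-school pupil correlation between baseline and postintervention, ρ = 0.6 (range 0.5–0.7). Correlation over time of the school effect, c, from 0.5 to 1. Within-country school ICC of 0.02 to 0.20; the stated 0.20 pools schools and countries, whereas the model removes country as a fixed effect.

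**The plan's own figure.** A two-sample comparison at d=0.30 needs about 175 per arm, 350 in all. With 200 per school the design effect is 1 + 199 × 0.20 = 40.8, giving 350 × 40.8 = 14,280 analysed. With 100 per school it is 20.8, giving 7,280. Doubling for 50% loss gives 28,560 or 14,560. The stated 6000 (3000 analysed) is reached only by solving for the unstated correlation: r of about 0.89 with 200 per school, or 0.77–0.79 with 100. So 6000 can be neither confirmed nor refuted, and it does not reveal which analysis was assumed.

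**Formulas.** With m pupils per school:

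- w = m·ICC / (1 + (m−1)·ICC)
- r = w·c + (1−w)·ρ
- Variance of the difference in change ∝ 2(1−r)
- Variance after efficient adjustment (pupil baseline plus school mean, or baseline means constrained equal) ∝ 1−r²
- Ratio, adjusted to change: (1+r)/2
- Pupil-level covariate alone ∝ 1 + ρ² − 2ρr

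**Results at m=59, ρ=0.6.** Equivalent extra schools = 51/ratio − 51. The last column is the power after adjustment if the change analysis had exactly 80%: Φ(2.80/√ratio − 1.96).

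| ICC | c | r | Ratio | Variance gain | Extra schools | Power |
|---|---|---|---|---|---|---|
| 0.20 | 1 | 0.975 | 0.987 | 1% | 0.7 | 80.5% |
| 0.05 | 1 | 0.903 | 0.951 | 5% | 2.6 | 81.9% |
| 0.02 | 1 | 0.819 | 0.909 | 9% | 5.1 | 83.6% |
| 0.20 | 0.8 | 0.787 | 0.894 | 11% | 6.1 | 84.2% |
| 0.05 | 0.8 | 0.751 | 0.876 | 12% | 7.2 | 84.9% |
| 0.02 | 0.8 | 0.709 | 0.855 | 15% | 8.7 | 85.7% |

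Over ρ = 0.5–0.7, the first row's ratio runs from 0.984 to 0.990. A 25% gain (17 schools, 90% power) needs r of about 0.5.

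**Pupil-level covariate alone.** At ICC 0.20 and c=1 its variance is 3.1–4.4 times that of the change analysis over ρ = 0.7–0.5. At c=0.9 it is 1.1–1.5 times. It beats the change analysis only if ρ > 2r − 1.

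**Simulation** (50 schools × 59 pupils, two time points, 1,500 replicates). Standard errors for change, pupil covariate alone, and pupil plus school mean:

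- ICC 0.20, c=1, ρ=0.5: 0.034, 0.068, 0.034
- ICC 0.20, c=0.8, ρ=0.6: 0.085, 0.086, 0.082
- ICC 0.02, c=0.8, ρ=0.6: 0.043, 0.040, 0.040

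The pattern agrees with the formulas. In the first case the theoretical 1–2% is not visible.

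**The case against.** Group×time in a mixed model is a standard, valid analysis, and the stated model implies a small loss. It has a single school intercept that does not vary over time. At ICC 0.20 the school effect then cancels from the change, and 1–2% of variance remains to be gained. This stands as a limit on size. It does not remove the point: a constant intercept is a modelling choice, not evidence that school effects do not drift, and the within-country ICC may be below 0.20.

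A reader might infer a gain of up to 25%, or 17 schools. That needs school means correlating only about 0.5 between baseline (November–March) and postintervention (May–August), and nothing in the article supports so low a value. A reader might also infer that adjusting for baseline can never increase variance. That is true of independent observations but false here for a pupil-level covariate on its own.

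The change analysis also has a merit of its own. Pupils were recruited knowing their school's allocation. If that produced a stable difference between arms, change scores remove it, whereas adjustment removes only part. This stands and is the reason to retain the stated model. The stated model also uses pupils without a baseline score, which the covariate form does only with imputation.

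Finally, the article says neither that the moderator is the SDQ total nor which time points the moderation models include. That part of the concern is conditional.

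**Conclusion.** The point holds as a matter of efficiency. The primary effect is a difference in change, and efficient baseline adjustment has variance (1+r)/2 relative to it, below 1 whenever r < 1. The expected gain is about 1–2% at ICC 0.20 with constant school effects, about 5–9% at a within-country ICC of 0.05 to 0.02 with constant school effects, and about 10–15% with school-effect correlation about 0.8. Larger gains need stronger drift. These figures rest on 59 pupils per school and ρ of about 0.6; the article gives no correlation over time and no within-country ICC.

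A reader might conclude that the planned analysis is biased or invalid. The documents do not support that. Nor is adjustment free of assumptions, because baseline followed unblinded allocation. The change is worth making because its cost is small, not because the loss is known to be large.

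**What to change.** Make the primary analysis a mixed model of mid-term and postintervention SDQ, with fixed effects for group, wave, group×wave, country, sex, age, the pupil's baseline SDQ and the school-mean baseline SDQ. Take the effect at postintervention. State that the school mean is a required term.

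An equivalent form keeps baseline as a response, constrains the arm means to be equal at baseline and adds a school-by-time random effect. It also retains pupils without a baseline score.

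Keep the stated unconstrained model as a sensitivity analysis, to cover a stable recruitment imbalance between arms. If baseline SDQ is used as a moderator, use the post-baseline model so that it is not also a response.

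The cost is analysis wording, fixed before the data are analysed. In the covariate form, missing baseline values also need simple imputation. No further data collection is required.

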**Methods and analysis:**

The IMPROVA intervention will be evaluated using a two-arm parallel group pragmatic cluster randomised controlled trial with an intervention and a wait-list control group. Secondary schools in France, Germany, Romania, and Spain were recruited. Originally, we estimated to enrol a total of 6000 students within 64 schools; that is, 16 schools per country. The IMPROVA programme is a multi-level intervention that provides tailored content for adolescents, families, and school staff. This content creates a unified and supportive framework that promotes mental health and social-emotional development among adolescents. A series of implementation strategies was planned to support the uptake of the programme into the education setting and among participants. Study outcomes were assessed at baseline, mid-term (during the intervention), postintervention (primary end point), and will be assessed at postintervention (secondary end-point; 6 months after postintervention). Overall mental health (Strengths and Difficulties Questionnaire) is the primary outcome. Secondary outcomes include: health-related quality of life, depression, anxiety, social isolation, and self-esteem. The trial will be evaluated regarding its effectiveness, cost-effectiveness, implementation, and social return on investment analysis.

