### Blinding, randomisation and allocation concealment

A statistician external to the IMPROVA project conducted the randomisation of schools into the intervention and control groups using a computer-based random number generator. The randomisation occurred before baseline assessments since we needed to be able to tailor the explanation and information of the project to participants according to their group allocation. For example, participants in the intervention group received a more detailed explanation on how to navigate the IMPROVA platform.

As planned, the statistician conducted a block randomisation at the country level in groups of four to eight schools, depending on the number of schools recruited at each trial site (country). In France, the second round of block randomisation needed to be adapted. In France, there are two types of secondary schools with distinct age groups of adolescents (collège: 11–14 years old; lycée: 15–18 years old); therefore, in the second round of randomisation in France, the randomisation was stratified depending on the type of secondary school to ensure an equal representation of younger and older adolescents in each group.

After the randomisation, the research team and participants were not blinded regarding school allocation.

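### The primary mixed model has no term for schools differing in change over time, so the standard error of its group×time effect is too small whenever such differences exist

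*Protocol article*

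**What the plan says.** Under Blinding, randomisation and allocation concealment, an external statistician "conducted the randomisation of schools into the intervention and control groups using a computer-based random number generator", so the school is the experimental unit.

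Under Effectiveness analysis, a linear mixed model is fitted to "continuous outcomes (SDQ total score) measured across three assessment points". Its fixed effects are time, group, group×time, country, sex and age, with further covariates possible. On the estimand: "The interaction term will be the main parameter of interest for assessing intervention effectiveness". The random part is "a random intercept for each participant to account for repeated measures, a random intercept for each school to adjust for within-school clustering". For this model the section names no school×time effect, school-level slope, robust variance or degrees-of-freedom method.

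Under Sample size, the calculation uses an "aggregated intra-class correlation of schools and countries of 0.20". On the error rate, the plan states: "All statistical tests will be two-sided, and a p value ≤0.05 will be considered indicative of statistical significance". The abstract and the Outcomes and assessments section both make the postintervention assessment the primary endpoint.

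**The concern.** In a school-randomised trial the error term for the treatment effect must include the variation between schools in whatever is being compared. Here that is change over time. A school intercept describes how schools differ in level, and a difference in level that stays constant is subtracted out of any change. The plan gives the school intercept the job of handling clustering, but for the parameter that decides the trial it does not do that job.

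The article itself gives reasons to expect schools to change differently. Baseline ran from November 2024 to March 2025 and postintervention from May to August 2025, so the interval could be about two to nine months and was fitted to school calendars. No component was compulsory. Communication was adapted to each school, and other well-being programmes could run alongside.

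If schools do drift, the primary confidence interval is too narrow and an ineffective programme can be declared effective more often than 5% of the time. The same applies to continuous secondary outcomes analysed with this model.

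**Working it through.** **Inputs from the article.** Participant and school random intercepts only; two-sided 0.05; 6000 pupils; 64 schools planned and 51 reported as recruited (the country counts 7 + 15 + 15 + 13 add to 50); pooled ICC 0.20; 50% refusal and loss.

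**Pupils per school (m).** 6000/64 ≈ 94. 6000/51 ≈ 118, and halving that if the 50% loss still has to come off the 6000 gives about 59. The article does not settle which reading applies. I use 59 and 94.

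**Assumed, because the article gives no value.** Pupil autocorrelation 0.6; school autocorrelation (the correlation of a school's effect between waves) 0.90 to 0.95; school-only ICC 0.01 to 0.20.

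**Formulas** (total variance 1, complete series):
- School×time variance: s = ICC × (1 − school autocorrelation).
- Pupil residual variance: e = (1 − ICC) × (1 − pupil autocorrelation).
- True variance of a school's mean change between two waves: 2s + 2e/m. The stated model can place s only in the residual, so it uses 2(s + e)/m.
- Ratio of true to model variance: D = 1 + (m − 1)ρ, with ρ = s/(s + e).
- Actual type I error: 2[1 − Φ(1.96/√D)].

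**The plan's own level.** With s = 0, ρ = 0 and D = 1, so the nominal 5% is reproduced.

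**One case in full.** ICC 0.20, school autocorrelation 0.90, m = 94: s = 0.20 × 0.10 = 0.02; e = 0.80 × 0.40 = 0.32; ρ = 0.02/0.34 = 0.0588; D = 1 + 93 × 0.0588 = 6.47; 1.96/√6.47 = 0.77; type I error 44.1%.

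**Type I error by assumption:**

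| School ICC | School autocorrelation | m = 59 | m = 94 |
|---|---|---|---|
| any | 1.00 | 5.0% | 5.0% |
| 0.01 | 0.95 | 5.8% | 6.4% |
| 0.01 | 0.90 | 6.7% | 7.8% |
| 0.02 | 0.95 | 6.7% | 7.8% |
| 0.02 | 0.90 | 8.5% | 10.6% |
| 0.03 | 0.95 | 7.6% | 9.3% |
| 0.03 | 0.90 | 10.3% | 13.4% |
| 0.05 | 0.95 | 9.5% | 12.2% |
| 0.05 | 0.90 | 13.9% | 18.7% |
| 0.20 | 0.95 | 23.8% | 31.6% |
| 0.20 | 0.90 | 35.1% | 44.1% |

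At m = 118 the figures are higher (48.5% in the last row). A check using the limiting variance components of the stated three-wave model gave the same values at m = 94 wherever both were run, with time either categorical or linear.

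**Incomplete series.** With an assumed 90%, 50% and 60% of pupils present at the three waves and m = 94, ICC 0.20 gives 24% and 36% at school autocorrelations 0.95 and 0.90. At 0.90, ICC 0.05 gives 14% and ICC 0.02 to 0.03 gives 9% to 10%.

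**How little drift is needed.** Type I error reaches 15% when ρ is 0.009 at m = 94 or 0.015 at m = 59.

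**Moderators.** In a null simulation (50 schools, 60 pupils each, ICC 0.20, school autocorrelation 0.90) the main contrast was rejected in 35% of trials and a sex×group contrast in 4.4%. A drift shared by all pupils of a school cancels when boys and girls of that school are compared.

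**The case against.** The strongest reply is that nothing in the article shows that schools drift. It gives no school×time variance and no correlation between waves; if schools move in parallel the stated model holds its 5%. This stands. A reader might infer from the pooled ICC of 0.20 that type I error is inflated several-fold as a matter of fact, or that about half of null trials would be declared positive. The documents do not support that. The 0.20 combines schools and countries, and country is a fixed effect in this model, so the school-only ICC may be well below 0.20 by an unknown amount. The higher rates also need a large m and full follow-up, whereas the plan allows for 50% refusal and loss and uses all available data, which leaves part of the intercepts in the contrast.

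A reader might also extend the concern to every moderator analysis. That fails for sex, age, socioeconomic status and baseline mental health in so far as they vary within schools and the drift is shared by a school's pupils. It applies to country and school type.

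Finally, time coding, contrast wording and degrees of freedom are commonly left to a statistical analysis plan, which may exist. This answers those details but not the main point, because the article fixes the random structure itself and assigns the school intercept a purpose it does not serve for the tested parameter.

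**Conclusion.** The structural point holds and follows from algebra: the stated random effects leave between-school variation in change out of the standard error of the primary parameter. The direction is certain whenever that variation exists.

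The size is not fixed by the documents. It runs from none, if schools do not drift, through a modest excess at small school ICCs, to a severe one only if the school-only ICC approaches the pooled 0.20. All figures above 5% rest on the assumed autocorrelations and on 59 to 94 pupils per school. Because the error lies in the primary test and small drift is enough to matter, it should be corrected before the outcome data are analysed.

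**What to change.** Add a random school×time effect to the primary model, either school×wave or an unstructured school covariance over the waves, with Satterthwaite or Kenward-Roger degrees of freedom for about 50 schools. Test the group×postintervention contrast as the primary parameter, which matches the declared endpoint. Use the same structure for continuous secondary outcomes and for school- or country-level moderators. A school-level analysis of mean change can serve as a check. Country×time fixed effects are optional.

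The cost is a change of model wording and a wider confidence interval. With 50 schools of 94 pupils, ICC 0.20 and pupil autocorrelation 0.6 (assumed), the standard error of the postintervention-minus-baseline contrast rises from about 0.024 SD to 0.046, 0.061 and 0.083 SD at school autocorrelations 0.95, 0.90 and 0.80. Multiplying by 1.96 + 0.84 = 2.80 gives a minimum detectable effect at 80% power of about 0.13, 0.17 and 0.23 SD, still below the planned 0.30.

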### Effect modification analysis

We will also evaluate whether the intervention effect varies according to certain characteristics such as participants’ sex, age, country, socioeconomic status, school type, and mental health status at baseline. These analyses will involve testing for statistically significant interaction effects between the intervention and potential moderators within linear mixed models.

### Mediation analysis

Mediation analysis will be performed using structural equation modelling to assess whether the effect of the intervention on the primary outcome is mediated by one or more intermediate variables (mediators) such as the secondary outcomes or other variables.

All available data will be included under the assumption that data are missing at random. All statistical tests will be two-sided, and a p value ≤0.05 will be considered indicative of statistical significance. Effect estimates will be reported with corresponding 95% CIs to indicate the precision of the estimates. The analysis will be conducted with SAS (V.9.4) and/or R software.

